**Fig. 2 Fig2:**
[figure not shown]
Flow chart of the trial process from allocation to follow-up at Kampala International University Teaching Hospital

**Fig. 3 Fig3:**
[figure not shown]
Standard Protocol Items: Recommendations for Interventional Trials (SPIRIT) figure of the trial schedule for enrollment, interventions, and follow-up/assessments at Kampala International Teaching Hospital

### Interim analysis

Biostatisticians will perform an interim analysis once we register a total of 36 patients for open hemorrhoidectomy using the two different anesthetic techniques, which is 62.1% of the planned number of patients. The primary, secondary, and tertiary outcomes will be evaluated to compare open hemorrhoidectomy using local anesthesia versus saddle block among patients with primary uncomplicated 3rd- and 4th-degree hemorrhoids.

The Data Monitoring Committee would recommend continuing, discontinuing, or modifying the trial, if concerns regarding the effect and safety of the participants will arise.

The recommendation to withdraw a patient from the trial will be decided by the principal investigator in case of failure of the anesthetic technique and loss of follow-up.

A recommendation of trial termination would be considered by the principal investigator, clinical trial institution, and ethics committee if achieving the difference in treatment effects is unlikely or if intolerable adverse effects occurred. The detailed results remain confidential to the investigator. The interim analysis was done on 10 March 2022, and continued recruitment was recommended.

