### Study variables

#### Primary outcome variable

The occurrence of pain following open hemorrhoidectomy will be determined in both groups using the area under the curve (AUC) for visual analog scale (VAS). The VAS will be used in an interval of 2, 4, and 6 h and 7 days postoperatively (the lower end of the scale labeled “0” means no pain while the upper end of the scale “10” signifies the worst imaginable pain).

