### Randomization and blinding

After fulfilling the enrollment criteria and obtaining the informed consent, the participants will be allocated randomly by assistant researchers well trained to either the local anesthesia group (group A) or the saddle block group (group B) by using envelope allocation concealment whereby half of the envelopes will contain a chit with letter A while the other half will have a chit with letter B signifying local anesthesia and saddle block, respectively. The content of the envelope will be opened once the patient is in the theater, and the patients and outcome assessors will be blinded about the anesthesia.

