### Data processing and analysis plan

Data will be statistically analyzed using IBM Statistics SPSS for Windows 23.0. The primary outcome will analyze all randomized patients (on an intent-to-treat (ITT) basis) and per-protocol (PP) population. The mean pain scores at rest and their standard deviations will be computed and compared using one-way ANOVA tests. VAS will be stratified as ordinal (0 as no pain, 1–3 as mild, 4–6 as moderate, and 7–10 as severe); the significance of the difference in the mean scores between local and saddle groups will be determined by the Kruskall-Wallis (*H*) test at 95% confidence interval, regarding *p* < 0.05 as statistically significant; furthermore, the mean pain scores will be analyzed for significant differences in the area under the curve (AUC) for VAS (2-sample *t*-test). The mean operative time and standard deviation will be computed for each technique of open hemorrhoidectomy. Cross tabulation will be performed between the two open hemorrhoidectomy techniques for categorical cost-effective analysis. The difference in the means will be compared using the *t*-test and their corresponding two-tailed p-value, regarding *p* < 0.05 as statistically significant.

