### Ancillary and post-trial care

The outcome of the study may indirectly help participants to obtain care during study time and will be recognized during publications. Diverse outcomes, e.g., too much pain, will result in converting from local to SA (crossover) and getting other analgesics other than those prescribed in the trial.

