### Trial discontinuation

The trial will be discontinued for individual patients due to non-adherence, e.g., not completing the specified duration of follow-up, diverse outcomes, e.g., too much pain resulting in converting from local to GA (cross over) and getting other analgesics other than those prescribed in the trial.

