### Unblinding

The recommendation to withdraw a patient from the trial will be decided by the principal investigator in case of failure of the anesthetic technique and loss of follow-up. In addition to that, outcome assessors will be blinded, and the criterion for unblinding is if they observe adverse effects related to intervention that needs to be disclosed to the attending clinician.

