### Missing data

Missing data will be reported as missing during the analysis. Clinical characteristics of those lost to follow-up and crossovers will be compared to those retained in both groups.

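### Withdrawal after randomization for failed anesthesia or pain-driven conversion contradicts the stated intention-to-treat analysis and may bias the pain comparison

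*Protocol article*

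**What the plan says.** Data processing and analysis plan: "The primary outcome will analyze all randomized patients (on an intent-to-treat (ITT) basis) and per-protocol (PP) population".

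Other sections of the Protocol article take patients out after allocation:

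- **Exclusion criteria** lists a failed anesthetic technique beside ordinary baseline exclusions.
- **Randomization and blinding** fixes the timing: "The content of the envelope will be opened once the patient is in the theater". The anesthetic is given after that.
- **Interim analysis**: "The recommendation to withdraw a patient from the trial will be decided by the principal investigator in case of failure of the anesthetic technique". **Unblinding** repeats the rule, with withdrawal "decided by the principal investigator in case of failure of the anesthetic technique and loss of follow-up".
- **Trial discontinuation** stops the trial for individual patients, one example being "too much pain resulting in converting from local to GA (cross over) and getting other analgesics other than those prescribed in the trial".
- **Missing data** says: "Clinical characteristics of those lost to follow-up and crossovers will be compared to those retained in both groups".

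Participant recruitment and study procedure has the principal investigator inject the local anesthetic and perform every hemorrhoidectomy. Study duration says in general terms that participants are followed for 7 days after surgery.

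**The concern.** An analysis of all randomized patients needs an outcome from each of them, whatever happened in theater. Here a patient can be excluded, withdrawn or discontinued because of an event that follows allocation. One of these events, pain severe enough to force conversion, is close to the primary outcome itself. The pain-conversion rule is written only for patients who start under local anesthesia, so losses may be unequal between arms.

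The decision to withdraw lies with the principal investigator, who injects one arm and operates on both and so knows the allocation. Blinding is claimed only for patients and outcome assessors.

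At stake is what the ITT result means. If the rules are applied as written and scores stop at withdrawal, the ITT set moves towards the per-protocol set. The two analyses then no longer check each other, which matters most in an equivalence trial.

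**Working it through.** **1. Can failure be known before randomization?** No. The envelope is opened in theater and the allocated anesthetic follows. Failure of that anesthetic is a post-randomization event, so it cannot work as an eligibility criterion.

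**2. Do the rules remove the patient, or only the treatment?** Interim analysis and Unblinding speak of withdrawal from the trial. Trial discontinuation ends the trial for the individual. Missing data sets crossovers against patients who were retained. No section says that VAS is still collected after these events or that the scores enter the ITT set. The 7-day follow-up statement in Study duration is general and does not mention withdrawn patients. Read literally, it conflicts with withdrawal and does not resolve it.

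**3. Is there an allowance for these losses?** Sample size determination raises 26 to 29 per arm, and 26 / (1 − 0.10) = 28.9, so 29 reproduces. The 10% is for loss to follow-up and non-response. Technique failure and conversion are not named.

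**4. How large could the shift be?**

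Inputs from Sample size determination: SD 2.356 (local) and 1.479 (comparator), δ = 0.73. Assumptions: the fraction removed, f, is 5%, 10% or 15% (the documents give no rate); scores are normal; the highest scores are the ones removed.

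Drop in an arm's mean = SD × φ(z) / (1 − f), where z is the (1 − f) quantile of the standard normal distribution.

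| f | φ(z)/(1 − f) | Local arm (× 2.356) | Comparator (× 1.479) | Net shift, both arms trimmed equally |
|---|---|---|---|---|
| 5% | 0.1086 | 0.26 | 0.16 | 0.10 |
| 10% | 0.1950 | 0.46 | 0.29 | 0.17 |
| 15% | 0.2743 | 0.65 | 0.41 | 0.24 |

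As a share of 0.73:

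- local arm only: 35%, 63%, 89%
- both arms equally: 13%, 23%, 33%

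In patients, with the highest scores of 29 removed from the local arm only, losing 1, 2, 3 or 4 lowers its mean by 0.19, 0.34, 0.47 or 0.60.

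**5. A milder model.** If the removed patients average d points above the rest of the local arm, the shift is f × d. At 10% removed, d = 2 gives 0.2 and d = 4 gives 0.4.

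The local-arm-only column is a ceiling for each f under this model. The equal-removal column is not a floor: if nobody is removed, or if converted patients score low, there may be no shift, and heavier loss from the saddle-block arm could reverse it.

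**The case against.** The strongest reply is that the analysis plan names both populations, so the removals may be meant for the per-protocol set alone, with everyone followed to day 7 and a telephone call as fallback. Ancillary and post-trial care also describes conversion as care given, without mentioning withdrawal. This is a possible intention, but the text does not state it: the rules say withdrawal from the trial, and failure stands among the exclusions.

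The reply does limit what can be claimed. Five stronger readings are tempting, and the documents do not support them:

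- **ITT analysis is impossible.** It is contradicted and undermined. It remains possible if scores are collected and kept.
- **Withdrawn patients' scores are coded as missing.** The Missing data section says how missing values are reported. It does not say that these patients' scores become missing.
- **The worst pain scores are removed.** This is an inference. Failure is seen in theater, the outcome is measured from 2 h afterwards, and a converted patient may score low early under the second anesthetic.
- **The bias favors equivalence.** That holds if local anesthesia is the more painful arm; otherwise trimming its high scores moves the estimate the other way. The technique-failure rules cover both arms, and the Introduction lists failed block among the problems of saddle block.
- **Any extra analgesic leads to removal.** The rule concerns analgesics outside the trial. Diclofenac rescue under the protocol does not trigger it, and the wording leaves open whether other analgesics suffice without conversion.

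**Conclusion.** The contradiction stands and rests on the article's own wording. An analysis of all randomized patients cannot sit beside an exclusion known only after randomization and withdrawals from the trial for failure or pain-driven conversion, with nothing said about keeping those patients' scores. It should be corrected before the ITT result is relied on.

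Confidence is high for the contradiction and low for the size and direction of any bias. At an assumed 5% to 15% removed, the shift in mean VAS runs from about 0.10–0.24 (equal trimming of both arms) to a ceiling of 0.26–0.65 (local arm only), against 0.73. These figures rest on an assumed rate, normal scores and removal of the highest values. They are also on the mean-score scale of the sample size section, whereas the primary outcome is an area under the VAS curve. A reader might infer that equivalence would be manufactured; the documents support only that the comparison may be biased.

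**What to change.** - Delete failure of the anesthetic technique from the exclusion criteria.
- In Interim analysis, Trial discontinuation and Unblinding, describe technique failure, conversion and non-trial analgesics as deviations from the allocated anesthesia. State that VAS is still collected at 2, 4 and 6 h and day 7. This concerns data collection only and leaves clinical care as it is.
- Analyze these patients in their randomized arm in the ITT set and leave them out of the per-protocol set only.
- Report failure and conversion by arm.
- For any patient already withdrawn on these grounds, include the VAS data already recorded and obtain the day-7 score where that is still possible. The documents report no such withdrawal; 45 patients were registered by 7 April 2022. Early scores not taken at the time cannot be recovered.
- Reconcile the two accounts of conversion: Ancillary and post-trial care has "too much pain, will result in converting from local to SA (crossover) and getting other analgesics other than those prescribed in the trial", while Trial discontinuation refers to GA.

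The cost is protocol wording and the completion of follow-up in what should be few patients: VAS at 2, 4 and 6 h and one day-7 contact each. The price in interpretation is that ITT scores will include the effect of the conversion anesthetic. The per-protocol analysis and the reported conversion rates help the reader to judge that effect.

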**Fig. 1 Fig1:**
[figure not shown]
Local anesthesia infiltration [20]

With this technique, the mixture will fill the inter-sphincteric space and block the inferior rectal branch of the pudendal nerve (S2, S3) and the perineal branch of the 4th sacral nerve, causing paralysis of the external sphincter.

For group B patients, the back will be cleaned with 70% alcohol and draped while in a sitting position. The anesthetist or the anesthesiologist will identify the L4/L5 interspace by anatomical landmarks. Lidocaine will be infiltrated in the skin and subcutaneous tissue to form a wheel in the skin. A 25-G quincke spinal needle will be introduced into the sub-arachnoid space using either the midline or paramedian approach as deemed necessary by the anesthetist. Once the free flow of cerebrospinal fluid is observed in the hub of the needle, 1.5 ml of 0.5% bupivacaine will be administered. The patient will be kept in the sitting position for 10 min and thereafter placed in supine. Time 0 will be reordered once the cleaning of the back starts.

After the proof of the effect of anesthesia is administrated, participants in both groups will be put in lithotomy position, and the perianal region will be cleaned and draped before the beginning of open hemorrhoidectomy which will be done by the principal investigator. The technique for open hemorrhoidectomy will be as described by Milligan Morgan Clinic [21] after which dressing will be done, and this will be documented as a time finale.

Analgesia will be given according to the visual analog scale (VAS) once it is rated more than 4 by the patient at 2, 4, and 6 h for all patients irrespective of the type of anesthesia, and all participants will be discharged based on the post-anesthesia discharge scoring system (PADS) for determining home-readiness whereby the patient is judged fit for discharge when his score is ≥ 9 [22] and the 7th day assessment will be done after the patient is called back by the research assistants. Participants will be reassessed using the VAS on the 7th day postoperative. Diclofenac sodium 100 mg oral 8 hourly for 5 days will be considered as rescue analgesia postoperatively. All patients will be receiving a tablet of metronidazole 400 mg 8 hourly for the following five postoperative days.

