### Trial status

The first case was recruited on 2 December 2021, and as of 7 April 2022, 45 patients were registered out of the required sample size of 58 for this protocol version 3 as of 21 May 2022.

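### The literal wording of the interim section leaves the by-arm results with the investigator, and nothing withholds them from the principal investigator, who gives the local anesthetic and operates in both arms

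*Protocol article*

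**What the plan says.** All of the following is in the protocol article.

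- **Timing** (*Interim analysis*): biostatisticians analyze the data "once we register a total of 36 patients for open hemorrhoidectomy using the two different anesthetic techniques, which is 62.1% of the planned number of" [...].
- **Content** (*Interim analysis*): "The primary, secondary, and tertiary outcomes will be evaluated to compare open hemorrhoidectomy using local anesthesia versus saddle block". This is a comparison between arms, not a pooled review.
- **Access** (*Interim analysis*): "The detailed results remain confidential to the investigator".
- **Decisions** (*Interim analysis*): the Data Monitoring Committee recommends continuing, stopping or modifying. Termination is "considered by the principal investigator, clinical trial institution, and ethics committee if achieving the difference in treatment effects is unlikely", or if there are intolerable adverse effects. On individual patients, "The recommendation to withdraw a patient from the trial will be decided by the principal investigator", the grounds being failed anesthetic technique and loss to follow-up. *Unblinding* repeats this.
- **The principal investigator's part in treatment** (*Participant recruitment and study procedure*): this person gives the local anesthetic mixture. After Fig. 1, both groups go on to "open hemorrhoidectomy which will be done by the principal investigator".
- **Blinding** (*Randomization and blinding*): patients and outcome assessors are blinded. The operator is not listed.
- **Status**: the interim was done on 10 March 2022, with a recommendation to keep recruiting. *Trial status* adds that by 7 April 2022 "45 patients were registered out of the required sample size of 58".

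**The concern.** The operator necessarily knows each patient's arm. By-arm interim results would add knowledge of which arm is ahead on pain, operative time and cost. Someone who has that knowledge and still has patients to treat may, without intending to, change the care taken over infiltration, the pace of surgery, or the threshold for calling a technique failed and withdrawing the patient. The first two bear on performance and on operative time, the secondary outcome. The third bears on who remains in the per-protocol population.

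The design is declared an equivalence trial. A change in behavior that narrows a gap seen at the interim would move the result toward the hoped-for conclusion, so the bias cannot be assumed to be conservative.

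A Data Monitoring Committee is already named in the same section, so there is a body that could hold the results instead.

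**Working it through.** **1. The plan's own figure.** The interim number is 36 (*Interim analysis*) and the planned total is 58 (*Trial status*; 29 per arm).

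36 / 58 = 0.6207 = 62.1%, as stated.

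**2. Upper bound on patients after the interim.** If the trigger was met, 36 or more were registered by 10 March 2022. Therefore at most 58 − 36 = 22 patients follow it, and 22 / 58 = 37.9%. This is a ceiling. The primary outcome includes a day-7 pain score, so if the analysis waited for that score in all 36, more than 36 may have been registered by 10 March.

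**3. Lower bound.** 45 were registered by 7 April 2022, after the interim. If the target of 58 is reached, the remaining 58 − 45 = 13 certainly follow it, and 13 / 58 = 22.4%.

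**4. Between the interim and 7 April.** At most 45 − 36 = 9 were registered in this interval, by the same reasoning as in step 2.

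**5. Plausibility of the dates.** The first case was recruited on 2 December 2021. From then to 10 March is 98 days, and to 7 April 126 days. Assuming even accrual, 45 × 98 / 126 = 35 registered by 10 March, close to the trigger of 36. The true share after the interim may therefore lie near the ceiling, but the protocol does not give the count on that day.

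**6. The access sentence beside the roles.**

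| Reading of the access sentence | Consequence |
|---|---|
| Results are held by the investigator (literal) | No sentence excludes the principal investigator, so the operator may see by-arm results and go on treating patients |
| Results are kept from the investigator | The sentence says the reverse of what is meant and must be corrected |

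The sentence needs changing on either reading.

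**The case against.** The strongest reply is that the protocol does not establish that the operator saw anything. The English is loose in places, so one preposition cannot carry much weight, and the sentence says only the investigator where its neighbors say principal investigator. Biostatisticians run the analysis, the committee recommends, and the only reported outcome is that recruitment should continue. All of this fits a principal investigator who received only the recommendation. **This stands**: the plan permits the flow of results but does not prove it.

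A reader might infer sight of the data from the termination rule. The text is "A recommendation of trial termination would be considered by the principal investigator, clinical trial institution, and ethics committee", and a recommendation can be considered without by-arm results, jointly with two other bodies. The effect-based ground makes the literal reading more natural but does not settle it.

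A reader might also infer that the operator controls the operative-time clock. The protocol says the dressing is done and the time documented, without saying who records it. In the saddle-block arm the interval also includes the anesthetist's procedure and 10 minutes of sitting. The operator therefore influences the secondary outcome only in part.

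Safeguards exist. Pain is rated by blinded patients and collected by blinded assistants separate from the recruiting team, infiltration sites and volumes are specified, and all randomized patients are analyzed by intention to treat as well as per protocol. These protect the primary outcome considerably. They do not cover operative time, the conduct of the procedure or the withdrawal decision.

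Finally, access rules often sit in a charter or full protocol that an article condenses. That would answer a complaint about silence. Here a rule is stated, and its wording is the problem.

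**Conclusion.** The point holds as one of wording and disclosure with a real route to bias. As written, the plan leaves by-arm interim results with the investigator and does not withhold them from the person who infiltrates, operates in both arms and decides withdrawals. It does not support saying that the results reached that person or that bias occurred.

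Between 13 (22.4%) and 22 (37.9%) of 58 patients come after the interim. The upper figure assumes only that the trigger of 36 had been met by 10 March 2022; the lower assumes that the target is reached. It would be wrong to read 22 as the count, or 9 as the minimum recruited between the interim and 7 April: both are maxima. The effect on the results cannot be quantified from the protocol and should be smaller for patient-rated pain than for operative time and withdrawals.

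**What to change.** **Wording.** Replace the access sentence in *Interim analysis* with, for example: *Interim results by arm are seen only by the biostatisticians and the Data Monitoring Committee. The principal investigator and trial staff receive only the recommendation to continue, modify or stop, together with any safety information needed for patient care.* The principal investigator can still consider a termination recommendation on that basis.

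**Disclosure.** The interim is done, the current version is dated 21 May 2022 and the study period ends on 31 May 2022, so rewording protects few remaining patients. State in the trial report who saw the March 2022 results by arm. If the operator did, tabulate operative time, withdrawals and pain scores by arm before and after 10 March 2022. Label the table descriptive: with one operator and at most 22 later patients it cannot separate interim knowledge from learning or time trend.

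**Cost.** The rewording and, if needed, one table. No extra staff are needed, because the biostatisticians and the committee are already named, and the sample size does not change.
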